**Methods and analysis:**

This multicentre trial, conducted at three University Hospitals in Stockholm and Uppsala, Sweden, consists of two phases: part 1 focuses on breast safety and is designed as a double-blind, randomised controlled trial. 260 postmenopausal women will be randomised to 100 mg mP or 0.5 mg NETA per day in continuous combination with 1 mg oestradiol. The primary objective is to compare the treatments with respect to percentage change in mammographic breast density after 12-month treatment. Secondary outcomes are breast proliferation, endometrial histology and proliferation, bleeding pattern, gut and vaginal microbiome, hormone levels and coagulation and metabolic factors, mood, and health-related quality of life. Part 2 features an open, single-arm design to study endometrial safety of 1-year treatment with mP in continuous combination with oestradiol on endometrial pathology (hyperplasia and cancer). We will treat 260 additional women with 100 mg mP/1 mg oestradiol resulting in an endometrial safety population of 390 women. The total number of participants in part 1 and part 2 will be 520.

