### Study assessments and procedures

The study will be performed at three university hospitals in Sweden: Karolinska University Hospital, Stockholm, Danderyd Hospital, Stockholm and Uppsala University Hospital, Uppsala. The study assessment and procedures are presented in table 1.

**Table 1 T1:** Study visit procedures

Test or procedures	Screening visit	Baseline visit	1-month contact	3-month visit	6-month visit	9-month visit	End of study visit	13-month contact
Informed consent	x							
Medical history	x							
Inclusion criteria	x	x						
Exclusion criteria	x	x						
Blood sample	x*	x†					x†	
Physical examination‡	x	x					x	
Gynaecological examination§	x	x					x	
Endometrial biopsy		x					x	
Mammography¶		x					x¶	
Breast biopsy**		x					x**	
Microbiota sample		x					x	
Questionnaire††		x		x	x	x	x	
Randomisation		x						
Compliance			x	x	x	x	x	
Vital signs‡‡				x	x	x	x	
Adverse events			x	x	x	x	x	x

* Safety parameters including hematologyhaematology, lipids, liver enzymes.

† Fasting blood sample for analysis of hormones, metabolic factors, and coagulation factors.

‡ Body weight, blood pressure, breast examination, cor, pulm.

§ Including vaginal ultrasound.

¶ A second mammography only in Ppart 1.

** Breast biopsies only in P part 1.

†† Depression and anxiety symptoms (PHQ-9, HADS), Hhealth-related quality of life (PGWB), Women’s Health Questionnaire ().

‡‡ Including bodyweight, blood pressure.

HADSHospital Anxiety and Depression ScalePGWBPsychological General Well-Being IndexPHQ-9Patient Health Questionnaire-9

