### Discontinuing study treatment

Subjects may be discontinued from study for any of the following reasons:

Development of exclusion criteria during the course of the study.Serious adverse event.Significant protocol violation.Unacceptable toxicity.Failure to comply with study evaluations/visits which would prevent evaluation of drug compliance and supply.Other conditions for which, in the investigator’s opinion, it is in the subject’s best interest to be withdrawn from the study.

When a subject withdraws from the study, the reason for the withdrawal shall be recorded. Any subject who prematurely terminates participation and has received at least one dose of study drug will undergo end-of-study procedures. If study participation is terminated due to an adverse event possibly related to the study drug or study examinations, the subject must be followed up according to the medical judgement of the investigator.

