### Outcomes

#### Mammographic breast density: primary outcome in part 1

Full-field digital mammography at baseline and after 12 months of treatment comprises mediolateral oblique and craniocaudal views of both breasts. Abnormalities will be evaluated on both views of each breast. In addition to visual judgement, a computer-based quantitative assessment will be performed. All mammograms will be pseudonymised so that the assessor will be unaware of the patient’s identity and type of treatment. The dense area on the right craniocaudal view image will be measured by using a commercial computer-assisted programme. A computer then records the number of pixels that fall within the defined areas according to the methodology described and used by us previously.^27^,^30^ Percentage change in mammographic density will be evaluated and compared between groups.

#### Breast cell proliferation: secondary outcome in part 1

Core needle breast biopsy from the upper lateral quadrant of the right breast will be taken after local anaesthesia at baseline and after 12 months of treatment. Ultrasound is used to identify areas with fibroglandular tissue. All women will be biopsied at the Mammography unit, Karolinska University Hospital. Tissue samples are paraffin-embedded and sectioned at 5 µm until analysis. Slides will be stained for the proliferation marker Ki-67 and other markers related to proliferation and apoptosis (caspase-3, p53 and bcl-2), and steroid hormone receptors. In addition to standard immunohistochemistry, a quantitative image analysis will be performed using a Leica microscope and Sony video camera connected to a computer with an image analysis system (Leica Imaging System, Cambridge, UK).^27 31^ Percentage change in breast cell proliferation will be evaluated and compared between the groups.

#### Endometrial assessment: secondary outcome in part 1 and primary outcome in part 2

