#### Statistical analysis

Analyses of primary and secondary outcomes will be based on an intention-to-treat (ITT) population (all subjects who have received at least one dose of study drug with a baseline evaluation meeting the entry criteria), as well as per-protocol population (subjects who have completed the study without major protocol deviations). The safety analysis population will comprise all patients who received at least one dose of the study drug.

The primary outcome variable mammographic breast density (part 1), expressed as percentage, will be compared between and within groups using the mixed model procedure with subjects as a random factor, and treatment (mP+E and NETA+E), time (baseline and exit) and treatment×time as fixed factors. Differences between groups will be evaluated by the interaction treatment×time, and differences within groups by the factor time, by holding the other factor (treatment) fixed.

Incidence of endometrial pathology (hyperplasia or cancer) in the mP+E group as endometrial safety (part 2) and based on histopathology will be expressed as incidence rate and 95% CI, in line with the European Medicines Agency guidelines.^43^

The secondary outcome variables (breast cell proliferation, endometrial cell proliferation, endometrial thickness using ultrasound, gene and protein expression of growth factors and apoptosis markers in breast and endometrial tissue, vaginal and gut microbiome, blood levels of serum hormones, growth and metabolic factors, lipid profile, and coagulations factors) will be analysed using the mixed model procedure with the same factors as above. In case of positively skewed distributions of these variables, log transformation will be performed prior to the analysis.

The Mann-Whitney U test will be used to compare the groups with respect to the changes in the PHQ-9, HADS, PGWB and WHQ and the Wilcoxon matched pairs test for changes in these variables within the groups.

If missing data occur in the ITT analysis, the method last observation carried forward (LOCF) will be used. Assuming missing data occur at random, patients with missing data can be included in the mixed model analysis, otherwise, we use the LOCF procedure. Correlations will be assessed by Spearman’s rank correlation test. A p<0.05 will be considered significant.

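### The primary model's only follow-up level is an undefined exit, so early-exit mammograms can be pooled with 12-month ones in the ITT contrast

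*Protocol article*

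**What the plan says.** All places are in the Protocol article.

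- **Target.** The abstract gives the primary objective as "percentage change in mammographic breast density after 12-month treatment". The primary objective of part 1 and the Outcomes section agree; the latter plans "Full-field digital mammography at baseline and after 12 months of treatment".
- **Stopping.** The section headed "Discontinuing study treatment" opens with "Subjects may be discontinued from study for any of the following reasons". It describes leaving the study only, and no route for a woman who stops drug but stays in follow-up. It adds: "Any subject who prematurely terminates participation and has received at least one dose of study drug will undergo end-of-study procedures".
- **What those procedures include.** Table 1 marks mammography at the end of study visit, and its footnote limits the second mammogram to part 1.
- **Analysis.** Statistical analysis defines the ITT set by one dose plus a qualifying baseline evaluation. The mixed model has "time (baseline and exit) and treatment×time as fixed factors", and the treatment×time interaction is the group comparison. Missing values are handled by the mixed model if missing at random, otherwise by LOCF. A per-protocol analysis is also planned; the section does not say which population is primary.
- **Sample size.** 91 women per group for a 35% difference, raised to 260 in total for about 30% discontinuation and incomplete data.

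**The concern.** The outcome is defined at 12 months, but the model's follow-up level is called exit, and early leavers have an exit mammogram. Followed literally, these rules put a mammogram taken after a few days or weeks in the same cell as one taken after a year.

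The contrast would then depend on how many women leave, when, and from which arm. Randomisation balances the women at baseline; it does not balance the time at which each is measured. If one arm loses more women early, for example because of bleeding or breast symptoms, part of the observed difference would be a difference in exposure time. This is separate from the usual criticism of LOCF, because these values are observed, although LOCF could lead to the same place by carrying an early value forward.

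**Working it through.** **1. The chain of rules.** Early leaving after a single dose leads to end-of-study procedures; in part 1 these include a mammogram; the model has one follow-up level, called exit; no window, minimum exposure or time-on-drug term is given. If exit is instead read strictly as month 12, an early mammogram would still be the last observation where LOCF is applied. Only an unstated rule that sets early values to missing avoids the pooling.

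**2. The plan's sample size.** 91 / (1 − 0.30) = 130 per group, and 2 × 130 = 260, as stated. This inflation counts discontinued women as giving no usable value. The discontinuation and analysis rules appear to bring their values in, so sizing and analysis rest on different assumptions. The 91 itself cannot be re-derived because no SD is given.

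**3. Dilution, with equal early exit in both arms.** Let p be the share with an early-exit mammogram and f the fraction of the 12-month group difference present at that time. Both are assumed. The contrast is 35 × (1 − p(1 − f)).

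| p | f | Contrast (%) |
|---|---|---|
| 10% | 0 | 31.5 |
| 20% | 0 | 28.0 |
| 20% | 0.5 | 31.5 |
| 30% | 0 | 24.5 |
| 30% | 0.5 | 29.8 |
| 30% | 0.75 | 32.4 |
| 30% | 1 | 35.0 |

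The protocol calls a difference of at least 30% clinically relevant. At p = 30% the contrast falls below that when 1 − f > (1 − 30/35) / 0.30 = 0.476, that is, when f is below about 0.52.

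**4. Power.** Back-solving 91 per group (two-sided 5%, 80% power, normal formula) gives a standardised effect of (1.960 + 0.842) × √(2/91) = 0.415. With 130 per group all analysed and p = 30%, power is 65% (f = 0), 81% (f = 0.5), 87% (f = 0.75) and 92% (f = 1). It stays at or above 80% if f is at least about 0.46 at p = 30%, or about 0.18 at p = 20%. Leaving these women out gives back the planned 91 per group and 80%. So pooling may raise or lower power, and power is not the main argument.

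**5. Unequal early exit.** Suppose both treatments have the same 12-month change D, early-exit shares are p1 and p2, and an early value holds a fraction f of D. The arm means are D(1 − p1(1 − f)) and D(1 − p2(1 − f)), so their difference has size D × |p1 − p2| × (1 − f). With assumed shares of 40% and 20%, this is 0.20 × D at f = 0 and 0.10 × D at f = 0.5. The true difference is zero.

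**The case against.** **Coding of early values.** No sentence says that an early mammogram is coded as exit. The word may be shorthand for the visit described under End of treatment (12 months), and the sample-size inflation fits that reading. Visit windows are often left to an SAP or full protocol not shown here. This stands in part: the pooling is an inference. But the point is more than missing detail, because the stated procedures, the single follow-up level and the LOCF fallback together produce it unless an unstated rule intervenes.

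**Per-protocol set.** It largely avoids the mixing, since it is limited to women who complete. That stands, but it is selected on completion, which randomisation does not protect.

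**Size.** A reader might infer that the trial will lose up to 10.5 of its 35 percentage points (35 − 24.5) and that month-12 measurement would restore them. The documents do not support this. The 30% includes incomplete data, so it is a ceiling for p. The Discussion says density responds within a few weeks, so f may be high in women still on drug. A woman who stops in week 3 and is measured at month 12 has been off drug for about 11 months, and her value could show as little of the difference, or less.

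**Serum hormones.** A reader might also infer that exit hormone levels in early leavers are read off drug. The interval between last dose and exit visit is not stated, so this cannot be claimed.

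**Early examinations.** Restricting who has an early mammogram would alter clinical management at exit. The point does not require that.

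**Conclusion.** The point holds as a defect in how the primary time point is fixed, with the coding of early values as its one inferential step. The outcome is a 12-month outcome, the model level is an undefined exit, the discontinuation section does not distinguish stopping drug from leaving the study, and the sample size assumes that discontinued women contribute nothing.

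The size is unknown. The range of 24.5% to 35% at p = 30% rests on assumed p and f, a common SD and equal early exit in both arms. Unequal early exit is the more serious risk, because it can create a difference where none exists. The documents do not show that such imbalance will occur, nor that the primary result would be invalid. A change is advisable, and it is cheap on the analysis side.

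**What to change.** **Statistical analysis.** For the primary contrast, replace exit by month 12 within a stated window. Do not enter early-exit mammograms as month-12 values and do not let LOCF carry them into that slot. Treat them as missing in the mixed model under its missing-at-random assumption, and report them in a supportive analysis with time on drug.

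**Discontinuation section.** Reconcile heading and text so that stopping drug and leaving the study are distinguished. State whether women who stop drug but still consent are followed to month 12. Leave the examinations done at early exit as they are.

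**Target.** State it. A month-12 value obtained off drug answers a treatment-policy question, not one about 12 months on treatment, and it may reflect other hormone therapy started after stopping.

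**Cost.** The analysis rule is a wording change that can be fixed before the code is broken, and it can cover women who have already left. Some observed values leave the primary contrast, which then leans on missing at random. Any change to follow-up would need an amendment, since enrolment began in March 2022, and could not recover month-12 values for women already past that date.

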##### Secondary objectives

To compare the effects of 1-year treatment with mP versus NETA, both in combination with oestradiol on the following parameters:

Breast cell proliferation.Endometrial histology and proliferation.Endometrial thickness using ultrasound.Bleeding pattern.Gene and protein expression of growth factors and apoptosis markers in breast and endometrial tissue.Vaginal and gut microbiome.Blood levels of serum hormones, growth and metabolic factors, lipid profile, coagulations factors.Scores on validated questionnaires: depression and anxiety symptoms, health-related quality of life, Women’s health (menopausal symptoms).

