#### Three, 6 and 9 months visit

Physical visits will be performed at 3, 6 and 9 months for assessment of vital signs, body weight and blood pressure, compliance, drug tablet return and adverse events. Furthermore, the participants will fill in the same questionnaires as at baseline.

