#### End of treatment (12 months)

At end of treatment, the same investigations as at baseline will be performed with the exception of a second mammography, which will only be performed in part 1.

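### Questionnaires measured at five visits are tested by a rank test on an unspecified change with LOCF, which can bias the 1-year comparison in either direction and cost power

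*Protocol article*

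**What the plan says.** **Visits.** The protocol article's Table 1 schedules the questionnaires at baseline, 3, 6, 9 and 12 months. The section on the 3-, 6- and 9-month visits says "Furthermore, the participants will fill in the same questionnaires as at baseline", and the section on end of treatment says "At end of treatment, the same investigations as at baseline will be performed".

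**Objective.** Questionnaire scores are listed under Secondary objectives, introduced by "To compare the effects of 1-year treatment with mP versus NETA, both in combination with oestradiol on the following parameters".

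**Test.** Statistical analysis says "The Mann-Whitney U test will be used to compare the groups with respect to the changes in the PHQ-9, HADS, PGWB and WHQ", and within groups "the Wilcoxon matched pairs test for changes in these variables within the groups". It does not say which change is meant.

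**Missing data.** The same section says "If missing data occur in the ITT analysis, the method last observation carried forward (LOCF) will be used". The exception, assuming data missing at random, is that "patients with missing data can be included in the mixed model analysis, otherwise, we use the LOCF procedure". The questionnaires are not among the outcomes given the mixed model, so LOCF applies to them.

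**Early leavers.** Discontinuing study treatment says "Any subject who prematurely terminates participation and has received at least one dose of study drug will undergo end-of-study procedures".

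**The concern.** The plan already holds a method that uses incomplete records without filling them in. It gives that method to mammographic density, tissue markers and blood levels, which have a baseline and a 12-month value only, so there are no intermediate values to draw on. The questionnaires have up to three intermediate scores per woman and get a two-sample rank test plus LOCF instead.

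A score at month 3, or at withdrawal, is not a score after one year of treatment. LOCF labels it as one. If a material share of women leave early, the comparison of arms becomes a mixture of differences at several times, weighted by when women left and by how many left each arm. A plain change score also forgoes baseline adjustment, and the stated test comes with no effect estimate or confidence interval.

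At stake is the reading of mood, quality of life and menopausal symptoms in Part 1. These are secondary outcomes, but they bear on how the two regimens are compared.

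**Working it through.** **1. The plan's own figure.** Sample size calculation gives 91 women per group and about 30% loss. 91 / 0.70 = 130 per group, 260 in total, which reproduces. It is a figure for mammographic density. No power or precision is stated for the questionnaires.

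**2. Inputs.** From the protocol: 130 per arm, 1:1 allocation, five visits, two-sided 5%, about 30% loss. Assumed, because the protocol gives none: SD 1 at each visit, equal correlation r = 0.55 between visits, true 12-month difference 0.35 SD. Loss is even and equal in both arms, so 7.5% are last seen at each of months 0, 3, 6 and 9.

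**3. What LOCF estimates.** Expected difference as a share of the true 12-month difference = Σ (share last seen at visit k) × (effect at k / effect at 12).
- Effect builds linearly (0, 0.25, 0.50, 0.75, 1): 0.075 × 1.50 + 0.70 = 0.81, so 0.35 becomes 0.28 SD.
- Plateau from month 3 (0, 1, 1, 1, 1): 0.075 × 3 + 0.70 = 0.925, so 0.32 SD.
- Waning (0, 1.4, 1.3, 1.15, 1): 0.075 × 3.85 + 0.70 = 0.99, so 0.35 SD.

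Varying when the 30% leave gives shares of 0.76 to 0.85 (linear), 0.85 to 1.00 (plateau) and 0.90 to 1.20 (waning, including a stronger waning course).

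**4. Unequal dropout.** Take true 12-month changes of 10 and 8 (difference 2), a front-loaded course (0, 0.6, 0.8, 0.9, 1) and loss d spread evenly. The LOCF mean is m × (1 − d + d × 2.3/4) = m × (1 − 0.425d).

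| Loss, arm with 10 / arm with 8 | LOCF means | Difference |
|---|---|---|
| 20% / 40% | 9.15 / 6.64 | 2.51 |
| 40% / 20% | 8.30 / 7.32 | 0.98 |
| 30% / 30% | 8.725 / 6.98 | 1.75 |

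**5. Baseline adjustment.** With complete data, the variance of a change is 2(1 − r) and of a baseline-adjusted score 1 − r², a ratio of (1 + r)/2. That is 0.65, 0.75 and 0.85 at r = 0.3, 0.5 and 0.7.

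**6. Power on the inputs in step 2.** The SE of the LOCF difference is about √(2 × 0.925 × 0.90 / 130) = 0.113 (the 7.5% carried from baseline have change 0). For the linear course, 0.284 / 0.113 = 2.51, and Φ(2.51 − 1.96) = 0.71 for a t-type test. The rank test is a little lower.

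For the month-12 contrast of a longitudinal model with arm-by-visit terms and a common baseline mean, the SE is 0.121. So 0.35 / 0.121 = 2.89 and Φ(2.89 − 1.96) = 0.82. This does not depend on the effect at earlier visits.

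| Course | Mann-Whitney with LOCF (simulated) | Model, month 12 |
|---|---|---|
| Linear | 67–68% | 82% |
| Plateau by month 3 | 78–80% | 82% |
| Mildly waning | about 82% | 82% |

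**7. Sensitivity.** Over correlations of 0.4 to 0.7, the loss for the linear course was about 10 to 19 points. A separate simulation (0.4 SD, r = 0.5, 400 runs, loss at random) gave the rank test 73%, 84% and 88% for linear, plateau and waning courses. The model had 82% to 88% across those runs, a spread that is simulation error.

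**The case against.** The strongest reply is that a rank test is defensible for bounded scores. Clinically significant depression is an exclusion, so PHQ-9 and HADS may sit near the floor. The outcomes are secondary and unpowered, and the time point and effect estimate may stand in an analysis plan that is not shown. This has weight: it limits the priority of the point, and it is why the rank test should stay as a sensitivity analysis. It does not answer the point, because the article itself fixes both the test and the imputation rule.

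Four stronger readings are tempting and are not supported.

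- *The 3-, 6- and 9-month data are ignored.* The protocol names no time point and does not rule out tests at each visit, and LOCF uses those scores as fill-ins.
- *The 12-month difference is shrunk.* This holds if the effect builds up and loss is similar in both arms. Steps 3 and 4 show that it can also be preserved or inflated.
- *The questionnaires are the only outcomes with intermediate data.* Bleeding is recorded throughout, and weight and blood pressure are taken at visits.
- *Large precision is lost by not using the intermediate visits.* With complete data they add nothing to the month-12 contrast (SE 0.104 either way). With 30% loss they raise power only from 80.7% (baseline-adjusted completers) to 82.4%. The SE under LOCF (0.113) is even below the model's (0.121), because filled-in values count as observed. The model's advantage is that it targets the 12-month difference.

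Two further mitigations stand in part. Women who leave early are to have end-of-study procedures, which should yield an exit score, but that score is still not a 12-month score. The plan also has a per-protocol analysis, which is restricted to women who completed without major deviations.

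**Conclusion.** The concern holds in a conditional form. For outcomes measured five times, the protocol fixes a rank test on a change whose time point is not named, with LOCF for missing scores, while using a mixed model that tolerates data missing at random for outcomes measured twice. The 1-year comparison can be biased in either direction, and the direction cannot be known in advance.

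On the assumed inputs the power cost runs from about 15 points (82% − 67%, linear course) to about 2 points (plateau) and none (mildly waning). The size rests on an assumed correlation, effect and dropout pattern. It also rests on reading the 30% allowance as questionnaire loss, although it was set for mammographic density and covers incomplete data as well as discontinuation. If exit scores are collected and loss is small, the effect is small. The improvement is worthwhile because it is cheap, and it does not threaten the trial's primary conclusions.

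**What to change.** In Statistical analysis, replace the Mann-Whitney and LOCF wording for the questionnaires by one longitudinal model per instrument:

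- scores at 0, 3, 6, 9 and 12 months as outcome;
- visit and arm-by-visit terms, with a common baseline mean in the two arms;
- unstructured covariance, and no carried-forward scores;
- the month-12 contrast named as the test and reported with a 95% CI.

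Enter the exit score of a woman who leaves early at the time it was taken, not as a 12-month value. Keep the rank test on observed 12-month change as a sensitivity analysis. If scores cluster at the floor, use an ordinal longitudinal model with the same terms.

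The cost is wording only, with no new visits, data or participants. The downside is that a modelling assumption (approximately normal means at about 130 per arm, or proportional odds, with data missing at random) replaces a rank test for secondary outcomes that have no stated power.

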### Exclusion criteria

A history or risk factors for breast cancer, breast cancer in situ or abnormal mammogram at baseline as assessed clinically by a radiology expert.A history or risk factors for endometrial cancer or hyperplasia or abnormal/proliferative endometrial biopsy at baseline.Vaginal bleeding.Any concomitant medical treatment except for well-controlled hypertension, non-insulin-treated type 2 diabetes, asthma and hypothyroidism.History or the presence of or risk factor for cardiovascular disease including thromboembolic disorder or cerebrovascular disease.History or the presence of liver and gallbladder disease, familial hyperlipidaemia, epilepsy or classical migraine with aura.A history or the presence of clinically significant depression or other psychiatric disorder that might in any way compromise the performance of the trial or undermine its scientific validity.Porphyria, systemic lupus erythematosus and otosclerosis.Current use of MHT or local oestrogen treatment.Alcohol and/or drug abuse.Clinically significant findings on physical and/or gynaecological examination at baseline.Hypersensitivity to any of the study treatments.

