The bleeding pattern will be registered by the patient throughout the study by a digital mobile application. Gynaecological examination including transvaginal ultrasound to determine endometrial thickness, as well as endometrial aspiration biopsy, will be collected at baseline and after 12 months of treatment. In part 1, endometrial histology and changes in proliferation markers, such as Ki-67, growth factors and markers related to apoptosis, will be compared between the randomised groups.^32^,^34^In part 2, the incidence of endometrial pathology (hyperplasia or cancer) will be examined in all participants allocated to 12 months of daily treatment with 100 mg mP in combination with 1 mg oestradiol. Endometrial histopathology will be evaluated according to a structured histological classification by two pathologists at the Department of Pathology, Karolinska University Hospital blinded to treatment and time of biopsy. In case of disagreement in interpretation, a third pathologist, also blinded, should be called on to make the final determination. The following histological classification will be used in both part 1 and part 2: no/insufficient tissue for evaluation, atrophic endometrium, inactive endometrium, proliferative endometrium, secretory endometrium, menstrual type, simple hyperplasia, complex hyperplasia, atypical hyperplasia and carcinoma.^32^

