### Sample size calculation

#### Mammographic breast density: primary outcome in part 1

Based on data from the WHI study, it was shown that an increase in mammographic density by 1% during combined MHT corresponded to a 3% increase in risk of breast cancer.^42^ We estimated that a difference of at least 30% in treatment response between the groups would be clinically relevant. A power analysis based on our previous results,^27^,^30^ and assuming a 35% difference in treatment response, revealed that a patient material of 91 women/group would be sufficient to detect a significant difference in mammographic breast density between the groups at the 5% level (two sided) with 80% power. Considering the estimated rate of discontinuation and incomplete data (~30%), the target sample for this part of the study would be 260 patients.

#### Endometrial pathology: primary outcome in part 2

The reported 1-year background incidence rate for endometrial hyperplasia/cancer in postmenopausal women treated with authorised oestrogen/progestogen combinations is approximately 0%–1%.^18 19^ With a sample size of 300 women in the treatment arm mP+E, two or less women with serious adverse endometrial outcomes would result in an annual incidence of 0.67% or less with an upper bound of the one-sided 95% CI of 2.08% or less. Considering the estimated rate of discontinuation and incomplete data (~30%), the target sample for this part should be 390 patients, 130 women randomised to mP from part 1 and another 260 women from part 2.

The total number of patients in part 1 (n=260) and part 2 (n=260) will be 520.

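### As written, the LOCF rule for missing data counts women with no exit biopsy as free of hyperplasia and cancer, which understates the part 2 primary incidence and its upper bound

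*Protocol article*

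**What the plan says.** All references are to the protocol article.

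- **Population (Statistical analysis).** "Analyses of primary and secondary outcomes will be based on an intention-to-treat (ITT) population", with a per-protocol analysis alongside. Membership of the ITT set needs one dose taken and a qualifying baseline. No post-baseline biopsy is required.
- **Missing data (Statistical analysis).** "If missing data occur in the ITT analysis, the method last observation carried forward (LOCF) will be used". The next sentence allows women with gaps into the mixed model if data are missing at random, and otherwise returns to LOCF.
- **Endometrial analysis (Statistical analysis).** Hyperplasia or cancer in the mP group is reported as an incidence with a 95% CI. No model is fitted.
- **Entry (Exclusion criteria).** A woman is excluded for an "abnormal/proliferative endometrial biopsy at baseline".
- **Biopsy schedule (Table 1; Endometrial assessment under Outcomes).** Biopsies are taken at baseline and at the end of study only. The histological classification includes "no/insufficient tissue for evaluation".
- **Early leavers (Discontinuing study treatment).** "Any subject who prematurely terminates participation and has received at least one dose of study drug will undergo end-of-study procedures".
- **Sizing (Sample size calculation).** The precision statement assumes 300 women on mP and holds that "two or less women with serious adverse endometrial outcomes would result in an annual incidence of 0.67% or less". It puts the matching upper limit, one-sided at 95%, at 2.08%. The target of 390 is set to allow for about 30% dropout and missing results.

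**The concern.** LOCF needs an earlier observation that says something about the later one. Here the only scheduled earlier observation is the pre-treatment biopsy, which had to be free of pathology for the woman to enter. For a woman with no exit biopsy, LOCF therefore enters a result that could only be negative and that carries no information about the treatment.

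The error runs in one direction. It adds women to the denominator and can never add an event, so the more biopsies are missing, the safer the combination appears. For a safety incidence that is the wrong direction. The Discussion says that this combination has been evaluated for endometrial safety in only one previous study and that the results may feed into guidelines.

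The rule also disagrees with the sizing. The sample size section treats women without a result as lost and bases its precision on 300. LOCF would return them to the analysis as non-events.

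**Working it through.** **Inputs.** From Sample size calculation: 300 evaluable women, 2 events, one-sided 95% bound 2.08%, 390 enrolled on mP (130 from part 1 and 260 from part 2), about 30% loss. The documents do not forecast how many women will lack any exit biopsy, so that share is varied from 10% to 30% as an assumption.

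**Formula.** For x events in n women, the exact (Clopper-Pearson) one-sided 95% upper bound is the 0.95 quantile of a Beta(x + 1, n − x) distribution.

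**The plan's own figure.** x = 2, n = 300: incidence 2/300 = 0.67%, bound 2.084%. This matches the stated 0.67% and 2.08%, so the exact method on 300 women is what the sizing used.

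**What LOCF does.** Let n women have an evaluable biopsy and m have none. The evaluable incidence is x/n. LOCF reports x/(n + m), which is the evaluable incidence multiplied by n/(n + m). With n + m = 390, that factor is 351/390 = 0.90, 312/390 = 0.80, 300/390 = 0.77 or 273/390 = 0.70.

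**Results** (incidence, with exact one-sided 95% upper bound in brackets):

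| Women with no biopsy | Evaluable n | 2 events, evaluable | 2 events, LOCF on 390 | 3 events, evaluable | 3 events, LOCF on 390 |
|---|---|---|---|---|---|
| 39 (10%) | 351 | 0.57% (1.78%) | 0.51% (1.61%) | 0.85% (2.19%) | 0.77% (1.98%) |
| 78 (20%) | 312 | 0.64% (2.00%) | 0.51% (1.61%) | 0.96% (2.47%) | 0.77% (1.98%) |
| 90 (23%, the plan's 300) | 300 | 0.67% (2.08%) | 0.51% (1.61%) | 1.00% (2.56%) | 0.77% (1.98%) |
| 117 (30%) | 273 | 0.73% (2.29%) | 0.51% (1.61%) | 1.10% (2.82%) | 0.77% (1.98%) |

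The last two rows differ because 390 is 300 × 1.3, whereas a 30% loss from 390 leaves 390 × 0.7 = 273.

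**Two-sided version.** The analysis section does not say whether its 95% CI is one- or two-sided. With two events the two-sided 95% upper limit is 2.39% (n = 300) or 2.62% (n = 273), against 1.84% under LOCF on 390. The pattern is the same.

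**Coverage.** Assume that missingness is unrelated to pathology and that the true rate is 2.08%. The nominal 95% one-sided bound under LOCF then covers the truth about 87% of the time with 300 observed and 82% with 273. The bound on the observed denominator covers it about 98–99% of the time. At a true rate of 1% the LOCF coverage is about 95% and 94%, so the harm to coverage depends on the true rate and is greater at the higher one.

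**The case against.** **The LOCF sentence does not name the endometrial outcome.** That outcome has its own paragraph, which refers to regulatory guidelines, and LOCF appears later, next to the mixed model. The authors may have had only the continuous outcomes in mind, and the sample size section points to an evaluable denominator. This stands as to intent: a reader might infer that the investigators have chosen to impute biopsies, and the documents do not show that. It does not remove the defect. The rule covers the ITT analysis, that analysis covers all primary outcomes, and the only stated alternative is a model that is not used for this one.

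**Early leavers are due end-of-study procedures.** This stands, and it limits the size. A reader might infer that the planned 30% loss means a 30% fall in the reported incidence. The documents do not support that as an expectation, because the allowance includes women who stop early and should still be biopsied. LOCF acts only on women with no exit result, so 30% is a ceiling.

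**Insufficient samples.** A reader might infer that these too would be overwritten by the baseline result. The classification makes them a recorded category, and nothing says they are treated as missing. How they are handled is simply not settled.

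**A per-protocol analysis is also planned.** It largely avoids the problem, since it is restricted to completers. But the article does not say which population leads for endometrial safety, so the ITT figure would be reported as a primary result.

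**2.08% is not a decision threshold.** Correct. The table shows three events giving 1.98% under LOCF, and a reader might infer that a failing result would pass. The article gives 2.08% only as the bound that two events in 300 would produce and states no pass or fail rule.

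**Conclusion.** The point holds for the rule as written. Applied to the part 2 primary outcome, LOCF counts a woman with no exit biopsy as event-free, understates the incidence and its upper bound, and contradicts the basis of the sizing.

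The size depends on the share with no exit biopsy, which is an assumption. With two events, the bound is 1.78% to 2.29% on evaluable women across 10% to 30% missing, against 1.61% under LOCF. With three events it is 2.19% to 2.82%, against 1.98%. The direction does not depend on the assumed share. The LOCF figure would be right only if women without a biopsy truly had no pathology, and the design offers no evidence of that.

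This is a correction to a stated rule, not a request for detail that a fuller document might hold.

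**What to change.** In Statistical analysis:

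1. State that LOCF does not apply to the endometrial incidence.
2. Define the primary denominator as women with an evaluable on-treatment or end-of-treatment biopsy, plus any woman diagnosed with hyperplasia or cancer during the study.
3. Report how many women have a missing biopsy and how many an insufficient one, and give the exact CI.
4. Show the all-treated denominator only as a sensitivity analysis, labelled as counting women without a result as event-free.
5. Add a second sensitivity analysis restricted to biopsies taken at about 12 months. A negative biopsy after short exposure says less about one-year safety, but dropping such biopsies from the primary analysis while counting early positives would be a debatable convention.

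The cost is one paragraph of wording and a somewhat wider reported bound. No extra data collection or change in sample size is needed.
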